## Discussion

In a recent clinical trial by our group, the response of LDL-C to PS consumption was associated with SNPs in cholesterol 7 alpha-hydroxylase (*CYP7A1, rs3808607*) and apolipoprotein E (*ApoE*, *rs7412* and *rs429358*) [13]. This ongoing GenePredict-PS clinical trial is investigating if this previous association identified between the SNPs and the LDL-C response to PS consumption can be used in a predictive manner. Individuals with genosets that fail to reach significant reductions in plasma LDL-C levels in response to PS consumption will be classified as nonresponders, whereas those who do exhibit LDL-C lowering will be classified as responders (see predicted response in Table 3). Individuals who are classified by the genosets as responders could be advised to consider PS-added products for lowering their elevated blood total and especially LDL-cholesterol, while non-responders could be either recommended to modify the dose of PS or use other pharmaceutical or natural health products that may lower cholesterol through other pathways. Very few studies in nutrigenetics and nutrition have yet to explore recruitment of participants a priori based on genotype, let alone based on combinations of genotypes (genosets). Previously, the impact of *rs1801133,* a variant in the methylenetetrahydrofolate reductase (MTHFR) gene, on riboflavin supplementation and blood pressure has been explored [16]. In that trial, Wilson et al. were able to use an available population of 1427 patients with hypertension from which they were able to recruit individuals based on genotype. The strategy of recruiting directly from a previous genotyped population can be highly recommend given the difficulty that the current trial has faced with de novo recruitment from the general public. Recruitment of previously genotyped individuals may be the most suitable way a priori nutrigenetic studies can be carried out in a suitable fashion, especially if the studies will be recruiting based on genosets or polygenic risk scores [17].

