Therefore, the primary specific hypothesis of this study after these protocol amendments are 1) the genoset formed from *CYP7A1 rs3808607T/T* and *APOE E3/3* predict nonresponse*,* and 2) *APOE isoform ε4/−* and *CYP7A1 rs3808607 G/−* will independently predict response to PS consumption in a pattern that reflects the current gene-biomarker associations outlined in Table 1. For these hypotheses, response is being defined as a reduction in the LDL-C concentrations due to plant sterol consumption.

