The trial will use a priori recruitment of 64 individuals (Table 3) with the specific SNPs associated with responsiveness to PS at a) the University of Manitoba’s Richardson Centre for Functional Foods and Nutraceuticals (RCFFN) and b) Seven Oaks General Hospital (SOGH) in Winnipeg, Manitoba, Canada. The present trial will therefore select individuals from the general population with specific SNPs and then test their responsiveness to PS consumption. These responsiveness characterizations will generate the required data to validate the genoset-based classifications of responders and nonresponders.

Each treatment period will consist of 28 days, with a minimum washout of 21 days between periods. Figure 1 shows the schematic flow diagram of the trial protocol.

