## Sample size calculation and statistical analysis

The sample size, with a minimum of 20 participants for each individual genotype and *n* = 20–22 for each individual genoset, is based on previous work performed by this research group [13]. A power calculation was performed using PROC POWER SAS Institute (version 9.4) using the paired means statement to model the AB/BA crossover design (corr = 0.75, a = 0.05 and b = 0.80); based on an average reduction in LDL-C of 0.34 mmol/L resulting from PS consumption according to the meta-analysis findings of Demonty et al. [8], the standard deviations in LDL-C for placebo (0.67 mmol/L) and PS (0.7 mmol/L) from the MacKay et al. [11] and a correlation in LDL-C values of 0.75, which was an estimate based on variability in LDL-C concentrations over time from MacKay et al. [11] and on a within-persons correlation in cholesterol response to plant sterols [15]. From this power calculation, we determined that 18 participants would be needed for each genoset to detect a response, in the form of a significant reduction in LDL-C from placebo to plant sterol consumption period, in the group. Our objective was to test if each genoset would respond, with the hypothesis that the *CYP7A1 rs3808607T/T* and *APOE E3/3* genoset would not respond to plant sterol consumption with LDL-C lowering.

Given the crossover design, the study outcomes measures will be analyzed in a per-protocol population where only participants who received both treatment and placebo are included. The effects of treatment, comparing the endpoint values of the treatment and placebo periods, will be analyzed by the SAS MIXED procedure. Sequence and sex will be included in the model as fixed factors, while participants will be included as a random and repeated factor. Genoset and treatment by genoset will be included as fixed factors to assess the impact of the genoset on the treatment. The impact of the individual genotypes will also be investigated individually. Significant treatment-by-genoset or treatment-by-genotype effects will be examined by the SAS SLICE function, with Bonferroni correction for the number of slices. Treatment effect sizes by genoset or genotype, from significant interactions, will be compared by t test or ANOVA using the difference in mixed-model least squares means summary statistics for the treatment effect slices, with Tukey-Kramer adjustment for multiple comparisons [13].

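### The nonresponder label rests on a non-significant result in about 20 people, which cannot distinguish an absent LDL-C response from a smaller or imprecisely measured one.

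*Protocol article*

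**What the plan says.** The classification rule is in the Discussion of the protocol article: "Individuals with genosets that fail to reach significant reductions in plasma LDL-C levels in response to PS consumption will be classified as nonresponders". Genosets that do show LDL-C lowering are to be called responders.

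The section on sample size and statistical analysis matches this rule. It says "Our objective was to test if each genoset would respond", treats a response as a significant fall in group LDL-C from placebo to plant sterol, and hypothesises that ε3/ε3 T/T will not respond. The Background makes that nonresponse part of the primary hypothesis and adds that "response is being defined as a reduction in the LDL-C concentrations due to plant sterol consumption". Under Study design, the purpose is given as: "These responsiveness characterizations will generate the required data to validate the genoset-based classifications of responders and nonresponders".

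The same analysis section plans a treatment-by-genoset interaction in a mixed model. Slices by genoset are Bonferroni-corrected and examined when the interaction is significant, and effect sizes are then compared between genosets with Tukey-Kramer adjustment. Table 3 plans 20 people for ε3/ε3 T/T and 22 for each of the other two genosets. The article gives no smallest relevant reduction and no confidence-limit criterion for nonresponse.

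**The concern.** For ε3/ε3 T/T the research hypothesis is the null hypothesis, and the rule accepts it when the test does not reject. A non-significant result in 20 people has three possible sources: no response, a real but smaller response, or a full response that the group missed by chance. The rule gives all three the same label. The Bonferroni correction guards against claiming a response too easily, but it makes a non-significant slice more likely.

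The label matters because it is the trial's main product. The Discussion suggests that people in a nonresponder genoset could be advised to change their plant sterol intake or use other products. A genoset with half the average benefit could be reported as a validated nonresponder.

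**Working it through.** **Inputs** (all from the sample size and analysis section and Table 3)
- Planning effect: "based on an average reduction in LDL-C of 0.34 mmol/L resulting from PS consumption".
- "the standard deviations in LDL-C for placebo (0.67 mmol/L) and PS (0.7 mmol/L" mmol/L).
- "corr = 0.75, a = 0.05 and b = 0.80"; the last figure is read as power.
- Planned n: 20 (ε3/ε3 T/T), 22 and 22. Three genoset slices give a Bonferroni level of 0.05/3 = 0.0167.
- Assumption: a true reduction of 0.17 = 0.34/2 mmol/L stands for a real but smaller response. The documents give no such value.

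**Step 1. Reproduce the plan's figure.** SD of the paired difference = √(0.67² + 0.70² − 2·0.75·0.67·0.70) = √0.2354 = 0.485 mmol/L. A two-sided paired t test at 0.05 with a difference of 0.34 has power 0.800 at n = 18, so the stated 18 per genoset is correct. At n = 20 the power is 84%.

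**Step 2. Precision at n = 20.** Standard error = 0.485/√20 = 0.1085. The 95% half-width is t × 0.1085, which is 0.217 with pooled variance (61 df) and 0.227 with the group's own variance (19 df). A result just short of significance therefore has an upper limit of roughly 0.43 to 0.45 mmol/L, above the full planning effect.

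**Step 3. Chance that a real reduction is non-significant, interaction test ignored.** Noncentral t with noncentrality δ/0.1085; ranges run from 61 to 19 df.

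| True reduction | at 0.05 | at 0.05/3 |
|---|---|---|
| 0.17 | 66–68% | 81–83% |
| 0.34 | 13–16% | 25–31% |

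**Step 4. The same with the interaction test as a gate.** Simulation with n = 20/22/22, SD of the difference 0.485 and pooled variance on 61 df; interaction tested at 0.05, then the ε3/ε3 T/T slice at 0.05/3.

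| True effects (T/T, other two) | Interaction significant | Slice missed, given that | Both |
|---|---|---|---|
| 0.17, 0.34, 0.34 | about 19% | about 97% | about 18% |
| 0.34, 0.34, 0.34 | about 5% | about 37% | about 1.8% |

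With the slice at an uncorrected 0.05, the joint figures are about 18% and 1.5%.

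The gate makes the label much rarer. When it opens, however, a genoset that truly responds by 0.17 is almost always called a nonresponder.

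**Step 5. What a confidence-limit rule could show at n = 20.** If the true effect is zero, the chance that the upper limit of the two-sided 95% CI lies below a margin is:

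| Margin | Probability |
|---|---|
| 0.34 | 84–87% |
| 0.25 | 59–62% |
| 0.17 | 32–34% |

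For 80% probability at margin 0.17, n = 66 would be needed. A genoset with a true reduction of 0.17 would still fall below the 0.34 margin in about 32–34% of trials.

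**The case against.** The strongest reply is that the analysis section examines slices only after a significant interaction and then compares effect sizes between genosets, so the figures in step 3 overstate how often the label would be given. This stands in part. On the gated path mislabelling is about 18% of trials in the half-response case, and under 2% if all three genosets respond by 0.34. The Discussion rule does not repeat the gate, so both sets of figures are needed. The gate does not make the label valid, because an interaction shows that responses differ and not that one is zero.

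Three stronger readings are tempting but not supported:
- *Noisier data or smaller groups favour the label.* This is true without the gate and reversed with it. At true 0.17/0.34/0.34 the joint probability is about 32% if the SD of the difference is 0.30, 18% at 0.485 and 11% at 0.70. Halving the groups lowers it to about 11%.
- *The Background and the Discussion contradict each other on what a response is.* The Background gives the concept. The analysis section and the Discussion give the test of it.
- *Labelling individuals from a group result is an error.* Assigning a person the class of their genoset is what a genetic test is for, and the article says so.

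It is also fair that the advice to nonresponders is worded as a possibility and that the predictive test is a long-term goal. That softens the consequence but leaves the rule unchanged.

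**Conclusion.** The concern holds. As written, the rule confirms a primary hypothesis by non-significance in 20 people, and nothing else in the article supplies a margin or confidence limit to repair it. This is a stated rule, not a detail left to an unseen analysis plan. The sample size calculation is sound for its purpose, which is to detect a reduction of 0.34 mmol/L; it does not support a claim of no response.

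With a true reduction of 0.17 mmol/L, a wrong nonresponder label is given in 66–83% of trials if the gate is not applied, and in about 18% if it is. These figures rest on the plan's SDs and correlation, a two-sided test, full recruitment to Table 3 and the assumed half-size response. The correlation matters: ungated at 0.05 with 19 df, the 0.17 figure is 78% if it is 0.6 and 35% if it is 0.9.

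**What to change.** Replace the classification rule in the Discussion, and state the replacement in the analysis section, before unblinding:

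1. Rest the predictive claim on the estimated difference in treatment effect between ε3/ε3 T/T and the other genosets, with its 95% CI. The planned model already yields this.
2. Report the treatment effect and 95% CI for all three genosets whatever the p-values.
3. Report a non-significant genoset as *response not shown* or *inconclusive*.
4. Use *nonresponder* only if the upper confidence limit for the reduction lies below a smallest relevant reduction that the sponsor states in advance and justifies.

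The wording of the conclusion must match the margin. Excluding 0.34 mmol/L is feasible with 20 people but shows only a below-average response. A margin such as 0.17 would support a stronger claim, but the present group would meet it in only about a third of trials even if the true effect were zero.

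The cost is a change of wording, with no new participants or measurements. The downside is that some results now destined for *nonresponder* will be reported as inconclusive.

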### Trial status

This trial is ongoing and has been recruiting since July 2016. The trial is expected to continue until approximately June 2020. The current protocol number and date is version 5 and 20 July 2018, respectively. 

## Data Availability

The de-identified datasets, that will be used and/or analyzed during the current study will be available from the corresponding author on reasonable request.

## Abbreviations

ALT: alanine aminotransferase
AST: aspartate aminotransferase
BREB: Biomedical Research Ethics Board
BUN: blood urea nitrogen
BMI: body mass index
CVD: cardiovascular disease
*CYP7A1*: cholesterol 7 alpha-hydroxylase
DNA: deoxyribonucleic acid
D_2_O: deuterium water
DSM: Diagnostic Services Manitoba
EMSA: electrophoretic mobility shift assay
GGT: gamma-glutamyl transferase
HDL: high-density lipoprotein
LDL-C: low-density lipoprotein cholesterol
PS: plant sterols
RCFFN: Richardson Centre for Functional Foods and Nutraceuticals
SAS: Statistical Analysis Software
SOGH: Seven Oaks General Hospital
SNPs: single-nucleotide polymorphisms
TC: total cholesterol
TG: triglycerides
TMS: trimethylsilylation
VLDL: very low-density lipoprotein
